**Methods:**

This pragmatic cluster randomized controlled trial will be conducted between December 2019 and June 2021. We will randomize eight operational districts (clusters) in seven provinces (Kampong Cham, Kampong Thom, Prey Veng, Thbong Khmum, Kampong Chhnang, Kandal, and Kampong Speu) to either the control group (PCF) or the intervention groups (ACF using a seed-and-recruit model, ACF targeting household and neighborhood contacts, and ACF targeting persons aged ≥ 55 years using mobile screening units). The primary endpoints will be TB case notification rates, additionality, and cumulative yield of TB cases. The secondary endpoints include treatment outcomes, the number needed to screen to find one TB case, and cost-effectiveness outcome measures. We will analyze the primary and secondary endpoints by intention to treat. We will compare cluster and individual-level characteristics using Student’s *t* test and hierarchical or mixed-effect models to estimate the ratio of these means. The incremental cost-effectiveness ratio per disability-adjusted life year averted will also be considered as a benchmark to determine whether the interventions are cost-effective.

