### Outcomes

We will measure the following endpoints in all four arms. The primary endpoint will be the case notification rate in the intervention and control ODs during the study period. We define a TB case to be either bacteriologically confirmed (smear-positive identified by smear microscopy, culture, or rapid diagnostics approved by the World Health Organization (WHO)), smear-negative TB (two sputum samples tested negative and clinically diagnosed by a clinician—with abnormal CXR or no improvement in response to a course of broad-spectrum antibiotics), or extrapulmonary TB (presence of local symptoms such as enlarged lymph nodes, joint swelling, and Gibbus deformity and presence of general symptoms such as cough, fever, weight loss, and night sweats) [23]. This will be ascertained from the results of the screening and routine case notification data reported to the NTP. We will also determine: additionality, comparing the yield in each arm with its respective historical baseline (same period in the preceding year); and cumulative yield over the project implementation period. Secondary endpoints will include: the number of people needed to screen to detect one TB case; direct and indirect costs per TB case notified; and the treatment outcome of all people with TB in this study. These data will be collected on the aggregated form at the health center level or as reported by the project implementation team in each arm, except cost data, which will be collected from study participants in the baseline and follow-up surveys.

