### Data collection and management

#### Plans for assessment and collection of outcomes

For the primary endpoints, we will collect case notification data from the intervention implementers (CATA, KHANA, CENAT), the provincial health department, and health centers (Table 2). For the secondary endpoints, data on treatment outcomes will be collected from the health centers. To assess the number needed to screen, we will collect screening data and the number of TB cases diagnosed from the intervention implementers, the provincial health department, and health centers. Data on costs—direct and indirect medical costs [29, 30], intervention, diagnostics, and medications—will be collected from the intervention implementers and the baseline and follow-up surveys (Table 2). In the survey, we will document the baseline characteristics of new diagnoses found in all arms using a questionnaire. Information on age, gender, education level, occupation, number of family members and housing, smoking, alcohol use, drug use, TB history, and the presence of other comorbidities will be collected. We will adapt and contextualize the knowledge, attitude, and practice survey instrument tools developed by the WHO to collect information on TB knowledge, attitudes, and care-seeking behavior toward TB [31]. A short follow-up survey will be conducted at the end of the TB treatment period for each person with TB to collect information on missed doses, side effects, and other TB treatment-related costs incurred.

**Table 2 Tab2:** Endpoints and data collection

Study endpoint	Description	Data source
Primary endpoints		
Case notification rates (cases notified per 10,000 population per year)	Numerator: number of cases notified by the selected districts	Case notification data from CENAT
	Denominator: total population in the OD	Population statistics (Ministry of Planning/Department of Statistics/CENAT)
Additionality (additional number of cases reported compared to historical baseline)	Number of cases notified by the selected districts	Case notification data from CENAT
	Historical data (cases notified in the preceding 3 years)	Historical case notification data from CENAT
Cumulative yield (cases diagnosed per 1000 screened)	Numerator: number of cases reported by each arm	Program data In the control arm, data to be collected from the health centers monthly

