### Statistical methods

#### Statistical methods for primary and secondary outcomes

For the primary endpoints, we will compute TB case notification at the cluster level by dividing the total number of TB cases (all forms) notified by the selected ODs by the total population in each OD. Case notification rates will be presented as TB cases notified per 100,000 population per year. The difference in the total number of TB cases notified during the intervention period and the number of TB cases notified in the preceding 3 years will be computed to determine additionality. We will calculate the cumulative yield of TB cases by dividing the number of cases notified in each arm by the total number of people screened for TB. Cumulative yield will be presented as TB cases notified per 1000 individuals screened.

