#### Frequency and plans for auditing trial conduct

The research team will conduct at least two monitoring visits to each OD during the 1-year implementation period. Field supervisors will also conduct at least four monitoring visits (e.g., every quarter for KHANA arms where the intervention is spread over 1 year and at every screening session conducted by CATA and CENAT during the implementation period, respectively). During monitoring visits, we will review consent forms, completeness of the data collection forms, and compliance with the trial protocol. Any anomalies in recruitment and data will be followed up by the field staff. Interim analyses will be conducted by the data analyst who is otherwise masked to intervention allocation. Data, recruitment processes, and interim results will be monitored by the research team and reported to the DMC.

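### Additionality has two conflicting baselines, and the Statistical methods version sets a count over about one year against a three-year count, which is negative at every planned effect size if background notifications are stable

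*Protocol article*

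**What the plan says.** The protocol article describes additionality in four places.

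- **Abstract, Methods:** "The primary endpoints will be TB case notification rates, additionality, and cumulative yield of TB cases".
- **Outcomes:** the case notification rate is named as the single primary endpoint. Additionality is then introduced as something also to be determined: "additionality, comparing the yield in each arm with its respective historical baseline (same period in the preceding year".
- **Table 2 (Plans for assessment and collection of outcomes):** under primary endpoints, "Additionality (additional number of cases reported compared to historical baseline". Its inputs are cases notified by the selected districts and "Historical data (cases notified in the preceding 3 years".
- **Statistical methods for primary and secondary outcomes:** the calculation starts from "The difference in the total number of TB cases notified during the intervention period" and sets against it "the number of TB cases notified in the preceding 3 years will be computed to determine additionality".

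The section on auditing trial conduct gives the length of the intervention: "during the 1-year implementation period". Trial status gives recruitment from 18 December 2019 to about 31 December 2020. Table 1 marks interventions and notification counts from Q4 2019 to Q4 2020.

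**The concern.** The same endpoint has two baselines, one year and three years. The quantity compared also changes. Outcomes speaks of the yield in each arm, while Table 2 and Statistical methods use cases notified by the districts. These are different series: Table 1 lists district notifications and cases reported by each arm on separate lines, and Table 2 takes them from different sources.

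The three-year version also compares periods of unequal length. An analyst who followed it exactly would report a shortfall of cases for a strategy that had doubled notifications. An analyst who saw the problem would have to repair it, and the article does not say how. A one-year and a three-year baseline give different answers whenever notifications are drifting, so a choice made after the results are known could affect what is reported.

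**Working it through.** The article states no additionality figure, so there is nothing to reproduce. The check is on the formula.

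**Inputs**
- Window length T: 1 year (auditing section); 380 days / 365.25 = 1.04 years (Trial status, counting both end dates); at most five quarters = 1.25 years (Table 1).
- Relative increase e in notified cases (Sample size): 110%, 98% and 30% in scenario 1; 75%, 50% and 25% in scenarios 2 to 4.
- Background notifications N per district per year: not given. Assumed constant; the sign of the result does not depend on N.

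**Formulas**
- Outcomes baseline: N·T·(1+e) − N·T = N·T·e
- Statistical methods as written: N·T·(1+e) − 3N, which is zero at e = 3/T − 1

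**Results, in units of N**

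| True effect | Outcomes rule, T = 1 | As written, T = 1 | As written, T = 1.04 | As written, T = 1.25 |
|---|---|---|---|---|
| none | 0 | −2.00 | −1.96 | −1.75 |
| +25% | 0.25 | −1.75 | −1.70 | −1.4375 |
| +30% | 0.30 | −1.70 | −1.65 | −1.375 |
| +50% | 0.50 | −1.50 | −1.44 | −1.125 |
| +75% | 0.75 | −1.25 | −1.18 | −0.8125 |
| +98% | 0.98 | −1.02 | −0.94 | −0.525 |
| +110% | 1.10 | −0.90 | −0.82 | −0.375 |

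Break-even effects are 3/1 − 1 = +200%, 3/1.04 − 1 = +188% and 3/1.25 − 1 = +140%.

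**How far this depends on a stable background.** Take T = 1, set the trial year's background to 1 and let it change by g a year. The three-year total is then the sum of 1/(1+g)^k for k = 1, 2, 3. For the +110% effect the result, 2.10 minus that total, is −1.62 at g = −10%, −0.62 at +5%, −0.39 at +10% and about −0.01 at +20%.

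**If the three-year figure is read as an annual mean.** Now let N be the preceding year's count, with trend g before the trial. The mean is N·[1 + 1/(1+g) + 1/(1+g)²]/3. A count 30% above the preceding year is 1.30N.

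| Trend per year | Three-year mean | Additionality |
|---|---|---|
| −10% | 1.115N | 1.30 − 1.115 = 0.185N |
| −5% | 1.054N | 1.30 − 1.054 = 0.246N |
| 0 | 1.000N | 0.300N |
| +5% | 0.953N | 1.30 − 0.953 = 0.347N |
| +10% | 0.912N | 1.30 − 0.912 = 0.388N |

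**The case against.** The strongest defence is that nobody would sum three years. The sentence in Statistical methods does not say whether the figure is a total, a mean or a trend, Table 2 lists the three-year series as a data input, and the Background cites pilot gains against the preceding year. The authors probably intended an annualised comparison, and details of averaging can be left to an analysis plan. This stands as a guess at intent. It does not settle the matter, because two sections of the same article name different baselines and neither says the three-year figure is scaled.

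A second defence is that all arms carry a similar offset, so comparisons between arms suffer less than the sign and size within each arm. That is fair while district baselines are alike, and allocation is matched on population size and number of health centers. But the offset is a raw count that grows with the baseline. At T = 1, a district with a true +30% effect scores below an unchanged control district once its baseline is more than 2.00/1.70 = 1.18 times as large. The documents give no counts from which to judge whether that occurs.

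Third, data analysts are masked to allocation. This reduces the risk of a results-driven choice of baseline, but the choice is still unfixed when masking ends.

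A reader might infer more than the documents support:
- **That every arm must show a loss.** This holds only for roughly stable background notifications and the windows above. If the whole 19 months from December 2019 to June 2021 counted as intervention, T = 19/12 = 1.583 and the two largest effects would turn positive (+0.135N for +98%, +0.325N for +110%). Table 1, however, ends interventions and notification counts in Q4 2020.
- **That the 30% effect belongs to the mobile-screening arm.** Sample size gives the three pilot effects by organization, and no section links that figure to that arm.
- **That additionality is undisputedly primary.** Outcomes reserves that title for the case notification rate, whose calculation does not use this baseline.

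**Conclusion.** The contradiction is certain: one year in Outcomes, three years in Statistical methods and Table 2, with a change from yield to notified cases as well. Followed as written, the Statistical methods rule gives a negative result for every effect size in Sample size at windows of 1 to 1.25 years, from −0.375N to −1.75N for effects of 25% to 110%. That result assumes roughly stable background notifications. The sensible repair is not unique: for a +30% gain on the preceding year, the annual-mean reading gives 0.185N to 0.388N under trends of −10% to +10% a year, an assumed range. Because the abstract and Table 2 list the endpoint as primary, it should be corrected before analysis. The defect is in a definition, not in any reported number.

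**What to change.** Use one definition in Outcomes, Table 2 and Statistical methods. For each operational district, additionality is all-form cases notified by the district in the intervention window, minus the cases expected over a historical window of equal length and the same calendar months. Replace yield in each arm with cases notified by the district.

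For expected cases, choose either the preceding year, as Outcomes has it, or the three-year annual mean scaled to the window. Fix the choice before unmasking and report the other as a sensitivity analysis. Also express the result as a percentage of expected cases, so that districts of different size can be compared.

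State the window's dates and keep it to 12 months or less. Otherwise the same months one year earlier run into the intervention: by the Trial status dates, 18 to 31 December 2019 would fall in both periods, and by Table 1 all of Q4 2019 would.

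State as well whether additionality is primary, since Outcomes differs from the abstract and Table 2.

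The cost is wording only. Table 2 already plans to obtain the three-year notification series from CENAT; matching calendar months requires it by month or quarter, which the article does not specify.

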## Methods: participants, interventions, and outcomes

### Study setting

The sampling frame consisted of operational districts (ODs) without ACF interventions currently, and in the preceding 6 months from the project implementation date. Using data from the Demographic Epidemiological Model of Cambodia developed in collaboration with the National Center for Tuberculosis and Leprosy Control (CENAT) [5] and other health and demographic data from Cambodia [24, 25], eight ODs (Fig. 1) have been purposively selected to include ODs with high and low incidence to maintain as much balance as possible. The selection was also based on the number of health centers to increase the comparability and generalizability of study findings across the groups.

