### Assignment of interventions: allocation

#### Sequence generation

The unit of randomization will be the ODs (clusters). From the list of underserved ODs in Cambodia provided by CENAT, we will randomly allocate four ODs with high TB incidence and four ODs with low TB incidence to the intervention and control arms, matched by the population size and the number of health centers.

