#### Implementation

The population living in the selected ODs will be included in the respective cluster. There will be four arms (Fig. 1), and two clusters will be randomly allocated to each arm. As all interventions have been endorsed by the CENAT and conducted in Cambodia, participants will not be notified if they are part of the intervention or the control group.

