For the secondary endpoints, we will evaluate the treatment outcome of TB cases detected in this study according to the following categories: treatment completed (without evidence of failure); treatment failed (sputum smear remains positive at month 5 or later of treatment); died (death due to any reasons before and during treatment); lost to follow-up (people newly diagnosed with TB who do not initiate treatment or treatment course that is disrupted for 2 or more successive months); not evaluated (no treatment outcome data available); and cured (sputum smear converted from positive to negative in the final month of the treatment and on at least one earlier assessment at month 2 or month 5) [23]. The number needed to screen to detect one TB case in each arm will be calculated by dividing the total number of persons screened by the number of TB cases detected (i.e., the reciprocal of the absolute cumulative yield). Direct and indirect medical costs that will be incurred before and during health-seeking will be measured based upon the baseline and follow-up questionnaires. Costs for identification of presumptive TB cases and engagement with KAPs for screening, including training and meetings before initiating ACF activities, will be categorized separately from the costs for diagnosis using radiological/bacteriological means and management of people with TB. The incremental cost-effectiveness ratio (ICER) will be estimated by dividing the difference in total costs between trial arms by the difference in the total number of TB cases detected. The ICER per disability-adjusted life year averted will also be considered as a benchmark to determine whether the interventions are cost-effective.

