We will analyze the primary and secondary endpoints by intention to treat, and the analyses will be conducted in two stages. First, we will analyze and present primary and secondary endpoints using the cluster summary method. The baseline characteristics of all arms at the cluster level and individual-level characteristics at baseline and endline will be compared using Student’s *t* test and hierarchical or mixed-effect models to estimate the ratio of these means. As the ODs have several health centers, we will adopt a linear mixed-effects model adjusting for baseline measurements to account for clustering in the data. Individual-level data will also be incorporated into multivariable regression models to account for potential confounders differing by the trial arm and improve the precision of the risk ratios by accounting for intercluster variations. The impact of TB case-finding strategies on treatment outcomes will be evaluated using survival analysis to compare treatment success rates across the intervention and control arms. The study will be reported according to the Consolidated Standards of Reporting Trials (CONSORT) [33] statement (Additional file 3), the template for intervention description and replication (TIDieR) [34] checklist for intervention description and replication (Additional file 4), the Standard Protocol Items: Recommendations for Interventional Trials (SPIRIT) [35] statement (Additional file 5), and the Pragmatic Explanatory Continuum Indicator Summary-2 (PRECIS-2) [36] for pragmatic trials (Additional file 6). All statistical analyses will be conducted using STATA 14 (Stata Corp LP, TX, USA) and R (R Foundation for Statistical Computing, Vienna, Austria).

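### The ICER is defined on raw arm totals, so any remaining difference in district population or baseline notifications is counted as an effect of active case finding

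*Protocol article*

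**What the plan says.** Under Statistical methods for primary and secondary outcomes, the protocol article obtains the ICER by "dividing the difference in total costs between trial arms by the difference in the total number of TB cases detected". It adds that an ICER per DALY averted will serve as the benchmark for judging cost-effectiveness, without saying how that ratio is built.

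The same section treats effectiveness differently. The notification rate is found by "dividing the total number of TB cases (all forms) notified by the selected ODs by the total population in each OD", and for the endpoint analysis "we will adopt a linear mixed-effects model adjusting for baseline measurements". Additionality is also set against historical notifications.

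On the design, Implementation says: "There will be four arms (Fig. 1), and two clusters will be randomly allocated to each arm". Sequence generation says that "we will randomly allocate four ODs with high TB incidence and four ODs with low TB incidence to the intervention and control arms". It goes on to describe the districts so allocated as "matched by the population size and the number of health centers", and gives no tolerance for that matching. Study setting describes the districts as "purposively selected to include ODs with high and low incidence to maintain as much balance as possible".

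**The concern.** A difference of arm totals measures the effect of ACF only if the two arms would have had the same cases and the same routine costs without it. With two whole districts per arm, that depends on how closely the district populations and passive notification rates agree. The protocol corrects for both in its effectiveness measures but not in the ICER. The ICER denominator can therefore disagree with the trial's own effect estimate.

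Cost-effectiveness is a stated objective, and the Discussion ties it to decisions on scale-up. The error is largest where the ACF effect is smallest. In scenario 1 of Sample size, one strategy is expected to add 30% and the other two 98% and 110%. Unequal imbalances could therefore affect the comparison between strategies as well as each comparison with control.

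**Working it through.** The protocol states no ICER value, so there is no figure to reproduce. The check is algebra with an illustration.

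**Inputs from the protocol article**
- Effect e: 25% (scenario 4), 50% (scenario 3), and 30% and 110% (both scenario 1), all from Sample size.
- Baseline notification rate b: incidence of 302 per 100,000 with about 40% undetected (Background and rationale), so 302 × 0.6 = 181.2 per 100,000.

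**Assumed inputs (not in the document)**
- Control-arm population 400,000, so N0 = 400,000 × 0.001812 = 725 passive cases. This figure cancels from the ICER.
- Routine cost r = 150 per case (range 50 to 400) and ACF cost a = 1 per head (range 0.3 to 3), in arbitrary currency units.
- Cases detected are taken as cases notified.

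**Step 1: cases.** Let q be the ACF arm's expected passive notifications divided by control's.

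Raw difference = N0[q(1+e) − 1] = N0·q·e + N0(q − 1)

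The first term is due to ACF and the second is imbalance. At e = 30% and q = 0.9, the raw difference is 725 × 0.17 = 123, while ACF caused 725 × 0.9 × 0.3 = 196. About 72 cases are lost to imbalance alone.

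**Step 2: ICER when population differs.** Cost and cases both shift:

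Raw ICER = r + a·q / (b[q(1+e) − 1]); true ICER = r + a / (b·e)

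At e = 25%, the true value is 150 + 1/(0.001812 × 0.25) = 2,358. At q = 0.9, the raw value is 150 + 0.9/(0.001812 × 0.125) = 4,124.

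| Effect | True | Arm 10% smaller | Ratio | Arm 10% larger | Ratio |
|---|---|---|---|---|---|
| 25% | 2,358 | 4,124 | 1.75 | 1,769 | 0.75 |
| 30% | 1,990 | 3,072 | 1.54 | 1,562 | 0.78 |
| 50% | 1,254 | 1,569 | 1.25 | 1,084 | 0.86 |
| 110% | 652 | 708 | 1.09 | 613 | 0.94 |

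If the 10% difference lies in the baseline rate instead of the population, the ratios at 30% are almost the same (1.55 and 0.79). Over the assumed cost ranges at 30%, a 10% difference in either factor gives 1.34 to 1.58 (10% low) and 0.77 to 0.87 (10% high).

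**Step 3: where the ratio breaks down.** The raw case difference is zero at q = 1/(1+e): 0.80 at 25%, 0.77 at 30% and 0.48 at 110%. At q = 1, raw and true ICER agree.

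**Step 4: does scaling repair it?** Per head, the cost difference is r·b·e + a and the case difference is b·e. Their ratio is r + a/(b·e), which does not contain the population ratio. For population ratios from 0.8 to 1.2 it stays at 2,358, 1,990 and 652 for effects of 25%, 30% and 110%. A baseline-rate difference is not removed by scaling alone and needs the baseline adjustment as well.

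**The case against.** The strongest reply is that the design already deals with this. Incidence is balanced by drawing on four high- and four low-incidence districts, and population and health centers are matched. This stands as a reason to expect a smaller imbalance. It does not make the imbalance zero: no tolerance is given, balance is promised only as far as possible, and each arm has two districts.

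A second reply is that the sentence is the textbook ICER in short form, and that the general model covers secondary endpoints, of which the ICER is one. Scaling and uncertainty often do belong in an analysis plan. But the article names the quantities as totals, nothing links the model to the ICER, and a quotient of arm totals does not use the model's output. If it is shorthand, a sentence or two would settle it.

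A third reply is about size, and much of it stands. At the effects of 98% and 110% expected for two strategies, a 10% imbalance matters little.

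A reader might go further and infer that a modest imbalance could halve the ICER or reverse the cost-effectiveness conclusion. The documents do not support that:
- Looking only at extra cases overstates the error, because cost moves with arm size. At a 25% effect under the assumed costs, the ICER halves only when the ACF arm is about 40% larger: 150 + 1.4/(0.001812 × 0.75) = 1,180 against 2,358.
- Cost-effectiveness is to be judged on the ratio per DALY averted, whose construction is not described.
- A probability of a zero or negative case difference would need a between-district coefficient of variation. The article gives none, and treating districts as independent draws would ignore the incidence strata.

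**Conclusion.** The point holds as a badly fixed estimator for a secondary economic endpoint. The direction follows from the formula alone: any q other than 1 puts N0(q − 1) cases, and their costs, into the ratio as if ACF had caused them.

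The size in this trial is unknown, because district populations, baselines and costs are not in the document. Under the assumptions above, a 10% population difference moves the ICER by about +75% or −25% at a 25% effect, by about +54% or −22% at 30%, and by about +9% or −6% at 110%. The rule should be corrected. Nothing here shows that the trial's cost-effectiveness conclusion would be wrong.

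**What to change.** Replace the definition along these lines:
- Incremental cost is the difference between arms in cost per 100,000 population-years.
- Incremental cases are the baseline-adjusted notification rate difference from the primary analysis, over the same districts and time window.
- The ICER per case is the ratio of these two, and the same increments are carried into the ICER per DALY averted.
- The baseline period is named, because Outcomes uses the same period of the preceding year while Table 2 uses the preceding three years.

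Routine care cost follows case load, so the cost difference should be put on the same baseline-adjusted footing as the cases.

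Report uncertainty by propagating the model's cluster-level uncertainty or by sensitivity ranges. Do not bootstrap districts: two per arm allow only three distinct resamples (the first twice, the second twice, or one of each).

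The cost is a change of wording and slightly more analysis. Population figures and historical notifications are already listed among the data sources in Table 2. The downside is a wider stated uncertainty around the ICER.
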